#### Primary analysis

The primary end-point will be the proportion of men who have gonorrhoea detected in the oropharynx by NAAT at any time within 12 weeks in any specimen (saliva and/or oropharyngeal swabs). The proportion of men with oropharyngeal gonorrhoea detected will be compared between both groups. The 95% confidence intervals (CI) of the proportion of men with oropharyngeal gonorrhoea will be calculated based on the ‘exact’ binomial confidence intervals [106]. The two study arms will be compared using logistic regression. Multivariate logistic regression will be performed to adjust any imbalance of baseline characteristics and potential confounding factors. Men with symptomatic urethral gonorrhoea may attend clinical services between the two clinic visits and test positive for oropharyngeal gonorrhoea. Any positive oropharyngeal results will be included in the analysis unless they were taken within 3 weeks of treatment because within 3 weeks NAAT results may represent residual non-viable DNA from the previous infection [107].

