#### Inclusion criteria

Men who have sex with men and aged 16 years or above, and fulfil either (i) or (ii).(i)Men aged 16–24 years: tested positive or negative for oropharyngeal gonorrhoea by NAAT within the previous 30 days, as young MSM are at higher risk of oropharyngeal gonorrhoea [80].(ii)Men aged 25 years or above: tested positive for oropharyngeal gonorrhoea by NAAT within the previous 30 days, as this population has a higher rate of repeat diagnosis of gonorrhoea within 90 days [88].
Provide written informed consent.Provide consent for the research team to contact their health professional and/or GP to clarify the use and name of any antibiotics used during the study period.Have sufficient English language proficiency to understand the study requirements.Men co-infected with HIV or other STIs are eligible.

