### Sample size

Sample size and power calculations were performed using Stata to compare two proportions (version 13 Stata Corp., College Station, TX, USA) [92, 93]. A previous study has shown that about 10% of MSM had a repeat culture positive for gonorrhoea within 12 weeks after a culture positive for gonorrhoea [88]. With NAAT is a more sensitive test and its detection rate five times higher compared to culture [56], we assumed oropharyngeal gonorrhoea positivity by NAAT in the arm using mouthwash B to be 20% over 12 weeks. Table 1 shows the number of participants required to detect a 50% reduction in oropharyngeal gonorrhoea positivity from 20% in the control arm to 10% in the intervention arm with 5% significance level and 80% and 90% power respectively. Calculations were also based on a 55% and 60% reduction in oropharyngeal gonorrhoea positivity. To detect a 50% reduction in oropharyngeal gonorrhoea positivity with 80% power, a total of 438 men will be required (i.e. 219 in each arm). This is a conservative effect size because our pilot data suggest that a single-dose of mouthwash is associated with a five-fold decrease in detection of gonorrhoea [86]. To allow for up to 15% loss of follow up [94], we will recruit a total of 504 men, 252 in each group. This will ensure 80% power to detect a 50% reduction in oropharyngeal gonorrhoea positivity from 20% to 10%, and 90% power to detect a 50% reduction from 25% to 12.5%.

**Table 1 Tab1:** Sample size calculations assuming 20% in the control arm will have a positive NAAT for oropharyngeal gonorrhoea within 12 weeks

Efficacy of mouthwash	Oropharyngeal gonorrhoea positivity in the intervention arm	Number of participants	
		80% Power	90% Power
50% reduction	10%	438	572
55% reduction	9%	356	464
60% reduction	8%	294	380

Calculations were based on 5% significance level

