### Randomisation

#### Sequence generation

A computer-generated randomisation sequence with a block size of four will be generated using Stata (version 13 Stata Corp., College Station, TX, USA) and held by an independent biostatistician. A 1:1 randomisation ratio, with no stratification, will be used. Enrolled men will be randomised to one of the two arms of the study in equal proportions.

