### Statistical methods

Data will be analysed in Stata (version 13 Stata Corp., College Station, TX, USA). The primary analysis will be an intention to treat analysis for all those with at least one follow up swab. The demographic characteristics and sexual risk behaviours will be compared between the control and intervention arm to ensure the balance in the baseline characteristics in both arms [105].

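### Covariates for the primary logistic model are to be picked from observed baseline imbalance and an open list, and the plan does not say whether the unadjusted or adjusted estimate is primary

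*Protocol article*

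**What the plan says.** All references are to the protocol article.

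- **Sequence generation:** allocation is in blocks of four. "A 1:1 randomisation ratio, with no stratification, will be used".
- **Inclusion criteria:** men aged 16–24 may enter having "tested positive or negative for oropharyngeal gonorrhoea by NAAT within the previous 30 days", with the reason that young men are at higher risk. Men aged 25 or above must have tested positive in that window, with the reason that repeat diagnosis within 90 days is more frequent in that population.
- **Statistical methods:** demographic characteristics and sexual risk behaviours are compared between arms "to ensure the balance in the baseline characteristics in both arms".
- **Primary analysis:** the arms are compared by logistic regression. The next sentence reads: "Multivariate logistic regression will be performed to adjust any imbalance of baseline characteristics and potential confounding factors".

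The text names no covariate, sets no threshold for imbalance, and does not state which of the two regressions gives the primary result.

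**The concern.** Comparing baseline characteristics between randomised arms cannot ensure balance. It only shows which chance differences occurred. If those differences decide the covariates, the model depends on the data to be analysed. A chance difference in a variable unrelated to the outcome needs no adjustment, while a strong predictor is worth adjusting for even when it is balanced. The stated rule selects on the wrong property.

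Two matters are at stake. First, with an open covariate list and no named primary estimate, several results could each be presented as the main one. Second, the plan passes over two variables that its own eligibility criteria treat as markers of risk and that are known for every man before allocation.

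**Working it through.** **1. The plan's own figure.** Inputs from the Sample size section: "Calculations were based on 5% significance level", an effect "from 20% in the control arm to 10% in the intervention arm", and 80% power. Two-sided testing is assumed because it reproduces Table 1.

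Uncorrected size per arm:

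n₀ = [1.960·√(2·0.15·0.85) + 0.842·√(0.2·0.8 + 0.1·0.9)]² / 0.10² = (0.990 + 0.421)² / 0.01 ≈ 199, or 398 in total.

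With continuity correction:

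n = (n₀/4)·[1 + √(1 + 4/(0.10·n₀))]² ≈ 218.5, rounded up to 219, or 438 in total.

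This agrees with the plan, and all six cells of Table 1 reproduce (438/572, 356/464, 294/380). The target of 504 is 438 × 1.15 = 503.7. The planned size does not depend on the point made here.

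**2. How often an imbalance rule would act.** Take a binary baseline factor with 50% prevalence (assumed) and 219 men per arm. The standard error of the between-arm difference is √(0.25 × 2/219) = 0.048. A difference above 10 points is then about 2.1 standard errors, and it occurred in 3.6–4.1% of simulated trials. A 5% significance test for imbalance triggers adjustment in about one trial in twenty, however prognostic the factor is.

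**3. Simulation of the choices.** Setting: 438 men, 1:1 allocation (simple, not blocked), one binary prognostic factor with 50% prevalence, control risk 20%, treated risk 20% (6,000 null trials) or 10% (3,000 trials). The factor's odds ratio is assumed, because the documents give none. The imbalance rule adjusts only when p < 0.05 for imbalance, also an assumption.

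| Factor odds ratio | Power, unadjusted | Power, fixed adjustment | Gain (points) | Power, imbalance rule |
|---|---|---|---|---|
| 1.5 | 83.7% | 84.0% | 0.3 | 83.7% |
| 2 | 83.0% | 84.1% | 1.0 | 83.1% |
| 3 | 84.2% | 85.3% | 1.1 | 84.1% |
| 5 | 82.6% | 86.0% | 3.3 | 83.2% |

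Gains are taken before rounding. The Monte Carlo standard error is about 0.7 points for each power. The differences are more precise, since all models were fitted to the same simulated trials.

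A second simulation (2,000 trials per scenario, half the men enrolment-positive, risk ratio 0.5 in both strata) gave 83.0% rising to 84.8% for control risks of 28% and 12%, and 82.7% rising to 86.6% for 35% and 5%. The latter pair implies a factor odds ratio of (0.35/0.65)/(0.05/0.95) ≈ 10, which is an extreme case.

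Type I error over the four factor strengths in the table (Monte Carlo standard error about 0.3 points):

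| Procedure | Type I error |
|---|---|
| Factor fixed in advance | 4.3–5.3% |
| Adjust only if imbalance p < 0.05 | 4.3–5.5% |
| Better of unadjusted and adjusted | 5.0–6.2% |
| Best of 12 covariate sets | 5.7–7.0% |

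**4. Unadjusted and adjusted estimates differ in target.** The planned 20% versus 10% is a risk ratio of 0.50 and an unadjusted odds ratio of (0.10/0.90)/(0.20/0.80) = 0.44. In the simulation the same two risks corresponded to adjusted odds ratios from 0.443 (factor odds ratio 1.5) to 0.421 (factor odds ratio 5). The gap is small, but it is a further reason to name the primary estimate.

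**5. Can the data carry the model?** With average risk 15%, 438 men give about 66 events. Arm (1), a three-level factor (2) and a two-level site term (1) use four slopes, about 16 events each. Five separate sites would need seven slopes, about 9 events each, with four of the sites expected to open more than a year after the first (Trial status).

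**The case against.** The best defence reads the two sentences in order: an unadjusted logistic comparison as the primary result, then a multivariable model in support. That reading is plausible, but the plan does not state it, and it leaves the imbalance trigger in place for the second model.

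It can also be said that covariate lists belong in the statistical analysis plan, which is not shown. That would answer a complaint that no list is given. It does not answer this point, because the article states a rule for choosing covariates, and an analysis plan that followed it would inherit the fault.

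A third argument is that restricting the analysis to men with a follow-up swab could make the arms differ for reasons other than chance. That is possible, but covariates fixed in advance handle it at least as well as covariates picked on observed imbalance.

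Several stronger readings are tempting and are not supported:

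- **That age group and enrolment status are the strongest known predictors.** The inclusion criteria present both entry routes as high risk and rank neither. Site is nowhere called prognostic. Saliva and the research swabs are batch tested in one laboratory, which weakens the case for site, although local assays differ and local swabs may count towards the endpoint.
- **That the stated rule inflates type I error.** Applied mechanically it does not. Inflation needs a choice among results, which the plan permits by its vagueness but does not describe.
- **That post-randomisation variables will be adjusted for.** Behaviour and antibiotic use are also collected after baseline, and the open phrase does not exclude them, but nothing says they will be used.
- **That unstratified randomisation is a flaw.** Blocks of four without strata are valid for 504 men.
- **That an odds ratio will be reported as a risk reduction.** The section names no summary measure beyond the proportions and their exact intervals.

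**Conclusion.** The point holds in limited form. The plan selects covariates from observed imbalance and an open list, leaves the primary estimate unnamed, and omits two risk markers of its own that are known before allocation. This should be corrected, but it does not threaten the validity of the trial.

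The expected gain in power is about 0 to 4 points, with the upper end reached only for strong factors. These figures rest on an assumed 50% prevalence, on assumed factor strengths and on a single binary covariate. The exact model proposed below was not simulated. With covariates fixed, type I error stays near 5%, and the opportunity to choose a model after seeing the data is removed. That removal is the main benefit.

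**What to change.** Before unblinding, replace the adjustment sentence with a definition of one primary model:

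- Logistic regression with arm and a three-level baseline factor: 16–24 negative, 16–24 positive, 25 or above positive. Eligibility leaves no fourth cell.
- Site, in a form that avoids sparse cells, for example Melbourne Sexual Health Centre versus the other sites.
- No post-randomisation covariates and no selection on observed imbalance. The baseline table stays as description only.
- The unadjusted comparison as a sensitivity analysis.
- Optionally, a standardised risk ratio and risk difference from the adjusted model, to match the planned 20% versus 10%.

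The cost is wording in the protocol or analysis plan. Age, the qualifying NAAT result and site are already known for every man. The sample size and the randomisation scheme can stay as they are.

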#### Secondary analysis

The cumulative incidence of oropharyngeal gonorrhoea by week 12 will also be calculated. Treatment arms will be compared using survival analysis, clustered by each individual to allow for multiple events. Individuals who tested positive for oropharyngeal gonorrhoea during the study period will be treated and remain in the study until end of week 12. Individuals will contribute at least two time periods of follow-up (i.e. time between each test).

The proportion of men who have gonorrhoea detected in the oropharynx by culture within 12 weeks will also be calculated as a secondary outcome, the statistical approach will be the same used for the primary analysis. A sensitivity analysis will also be performed comparing treatment arms in terms of gonorrhoea detection at 6 or 12 weeks using repeated measures logistic regression methods.

The adherence to mouthwash over 12 weeks will be collected from the questionnaire every 3 weeks. The number of days using mouthwash over the 12-week period will be calculated for each participant, and stratified by treatment arm.

Acceptability and tolerability of using mouthwash over 12 weeks will be measured. Participants will be asked about any discomfort and difficulties in using the mouthwash every 3 weeks.

The proportion of men who have other STIs (i.e. gonorrhoea at other site except at the oropharynx, chlamydia, HIV and syphilis) by 12 weeks will also be calculated as a secondary outcome and stratified by treatment arm.

### Trial status

The trial commenced recruitment in March 2016 at the Melbourne Sexual Health Centre. It is expected recruitment will commence at other sites (Sydney Sexual Health Centre, Western Sydney Sexual Health Centre, RPA Sexual Health, Northside Clinic) in June 2017. It is expected this trial will be completed by December 2018.

### Ethical consideration

This study protocol has been approved by the Alfred Hospital Ethics Committee in Melbourne, Victoria (project number 29/16; HREC/17/Alfred/13).

## Discussion

The rising rates of gonorrhoea in MSM urgently require novel, safe and effective non-condom-based and non-antibiotic-based interventions to reduce the incidence of gonorrhoea that are not associated with generation of antibiotic resistance. Epidemiological, clinical and mathematical modelling data provide substantial evidence that the oropharynx is the key driver of gonorrhoea in MSM [52]. Recent laboratory data and an RCT have shown that a single-dose of mouthwash has a short-term inhibitory effect against *N*. *gonorrhoeae* in the oropharynx [86]. However, it is unclear whether daily use of mouthwash can prevent acquisition of oropharyngeal gonorrhoea and this will be the first multicentre RCT to evaluate whether daily use of mouthwash could reduce the risk of oropharyngeal gonorrhoea acquisition. If we show daily use of mouthwash is effective in reducing the prevalence and incidence of oropharyngeal gonorrhoea, this will be the first acceptable, widely available and easily implementable non-drug intervention for gonorrhoea control since the widespread use of condoms. Mouthwash is commonly used albeit not often daily [108], and it therefore has the potential to rapidly be implemented in the community. If this intervention is proven to be effective it will change national and international strategies for gonorrhoea prevention and control.

We have limited this trial to MSM only because oropharyngeal gonorrhoea is rare in transgender individuals and heterosexuals and transmission between men and women may less frequently involve the oropharynx [109–112]. The only group of heterosexuals where oropharyngeal transmission may play a significant role is female sex workers, particularly in Asian countries [113–115].

There has previously been some controversy about the use of mouthwash and increased the risk of oral cancer [116–118]. However, a review and a meta-analysis of epidemiological studies have shown there is no association between oral cancer and mouthwash use (including daily use, and alcohol-containing mouthwash) [119, 120]. This is therefore anticipated to be a completely safe intervention.

The aim of daily use of mouthwash is to reduce the prevalence and incidence of gonorrhoea infection in the oropharynx in order to reduce further ongoing transmission to their partners, but not as an alternative treatment for gonorrhoea. A recent modelling study has estimated that there would be a three-fold reduction in prevalence of oropharyngeal gonorrhoea if 50% of men use the mouthwash on 50% of days. In addition, if 75% of men use the mouthwash on 75% of days, it may achieve a scenario close to elimination from MSM populations [77].

Topical antiseptics have been used against STIs for more than 100 years, but only for genital infections [121]. This trial will be the first study to evaluate the role of topical antiseptics used against STIs other than genital infections. If we show that antibacterial mouthwash reduces oropharyngeal gonorrhoea infection, then these findings could lead to a widespread public health intervention to increase mouthwash use among sexually active MSM. The ultimate outcome may be a substantial fall in gonorrhoea among MSM and a reduced probability of new resistant gonococcal strains emerging.

## Abbreviations

HIV: Human immunodeficiency virus
HREC: Human Research Ethics Committee
MSM: Men who have sex with men
NAAT: Nucleic acid amplification test
NHMRC: National Human and Medical Research Council
OMEGA: Oral Mouthwash use to Eradicate GonorrhoeA
PrEP: Pre-exposure prophylaxis
RCT: Randomised controlled trials
SMS: Short message service
STI: Sexually transmissible infection
